## Abstract

Physical inactivity and declining health-related physical fitness among college students are growing global public health concerns. High-intensity interval training (HIIT) is a time-efficient strategy to improve multiple components of health-related physical fitness. Emerging evidence suggests that exercise timing may influence physiological responses and adherence through circadian rhythm regulation; however, its feasibility in college settings, particularly in China, remains unclear. This study aims to evaluate the feasibility and preliminary effectiveness of an eight-week time-specific HIIT programme among Chinese college students, and to compare outcomes between morning and evening training. In this mixed-methods feasibility randomized controlled trial, approximately 72 students with low physical activity levels and intermediate chronotype will be randomly assigned to a morning HIIT group, evening HIIT group, or control group. Intervention groups will complete three HIIT sessions per week for eight weeks. Primary outcomes include feasibility indicators (recruitment, retention, adherence, and data completeness). Secondary outcomes assess changes in body composition, cardiorespiratory fitness, muscular strength, endurance, and flexibility. Quantitative data will be analysed using descriptive and repeated-measures methods, while qualitative interviews will be thematically analysed. Findings will inform the feasibility and design of future large-scale trials and contribute to chrono-exercise research in college populations.

## 1. Introduction

In recent years, declining physical activity levels and deteriorating health-related physical fitness among young adults have become important global public health concerns [1]. College students represent a particularly critical population during the transition from adolescence to adulthood, a period in which long-term lifestyle behaviours, including physical activity patterns, are often established and maintained into later life [2]. However, modern academic environments characterised by increased academic pressure, prolonged sedentary learning, and extensive use of digital technologies have contributed to reduced physical activity participation among college students [3]. Insufficient physical activity in this population has been associated with a range of adverse health outcomes, including reduced cardiovascular fitness, increased risk of obesity, and poorer psychological well-being [4].

In China, the physical health of college students has received growing attention from policymakers and educational institutions [5]. National health surveillance reports have indicated a gradual decline in several health-related physical fitness indicators among Chinese college students, including endurance capacity, muscular strength, and overall participation in physical activity [6]. Although universities have implemented various physical education (PE) programmes and policies to address these issues, the effectiveness of traditional PE curricula has sometimes been limited due to factors such as low student engagement, insufficient exercise intensity, and a lack of innovative teaching approaches [7]. These challenges highlight the need for more efficient and attractive exercise strategies that can be realistically integrated into the daily routines of college students.

High-intensity interval training (HIIT) has emerged as a time-efficient exercise modality that can produce meaningful improvements in cardiorespiratory fitness, metabolic health, and overall physical performance within relatively short training durations [8]. Compared with traditional continuous aerobic exercise, HIIT requires less time commitment while still producing comparable or even superior physiological adaptations, making it particularly suitable for populations facing time constraints, such as university students. Consequently, HIIT-based exercise programmes have increasingly been proposed as practical interventions to promote physical activity participation and improve health-related physical fitness in young adults.

Beyond exercise modality and intensity, increasing attention has recently been directed toward the role of exercise timing in shaping physiological responses and training adaptations. Human physiological processes are regulated by endogenous circadian rhythms—approximately 24-h biological cycles that influence hormone secretion, metabolism, sleep–wake patterns, and physical performance [9]. Emerging evidence suggests that the timing of exercise relative to an individual’s circadian rhythm may influence acute physiological responses, exercise performance, and long-term training outcomes [10]. This concept, often referred to as chrono-exercise, proposes that aligning exercise timing with circadian biological rhythms may enhance training effectiveness and improve adherence to exercise programmes.

These circadian influences may be particularly relevant among college students, whose daily routines, academic schedules, sleep patterns, and physical activity behaviours are often irregular. Previous studies have shown that insufficient physical activity, sleep disruption, and circadian misalignment are associated with poorer physical health outcomes, reduced exercise participation, and lower physical fitness levels among university students [4,11]. Therefore, understanding whether morning or evening exercise produces different responses in this population may help optimize exercise interventions and improve adherence within university settings.

Individual differences in circadian rhythm are commonly described through chronotype, which reflects a person’s natural preference for earlier or later timing of daily activities and sleep patterns. Individuals may be classified as morning types, evening types, or intermediate types based on their circadian preference. Previous studies have suggested that chronotype may influence physical performance, motivation to exercise, and adherence to structured training programmes [11]. Consequently, the timing of exercise sessions may interact with circadian biology to influence both physiological outcomes and behavioural responses to exercise interventions. Figure 1, developed based on existing chrono-exercise and circadian rhythm literature [10,12,13], illustrates the proposed mechanistic pathway through which exercise timing (morning vs. evening HIIT) may interact with circadian alignment factors, including chronotype and endogenous biological rhythms, to influence exercise-related responses such as adherence, physical performance, and physiological adaptation. These responses are expected to contribute to improvements in health-related physical fitness outcomes, including body composition, cardiorespiratory fitness, muscular strength, muscular endurance, and flexibility.

Despite the growing interest in chrono-exercise, empirical evidence examining the feasibility and effectiveness of time-specific exercise interventions in university settings remains limited. Few studies have explored whether performing HIIT at different times of day such as morning versus evening may produce different health-related physical fitness outcomes or influence participants’ perceptions and experiences of the training programme. Understanding these factors is important for designing exercise interventions that are both physiologically effective and practically acceptable within real-world educational environments.

To address this research gap, the present study developed a structured HIIT module specifically designed for Chinese college students. Before implementing large-scale intervention programmes, it is essential to evaluate the feasibility and practicality of the training module within the target population. Feasibility studies play a critical role in the early stages of intervention development by assessing recruitment, adherence, acceptability, and implementation challenges within real-world contexts [14]. In addition to quantitative assessments of health-related physical fitness outcomes, qualitative methods such as semi-structured interviews can provide valuable insights into participants’ experiences, perceived benefits, and potential barriers related to the intervention.

Therefore, the present study aims to evaluate the feasibility and preliminary effect of an eight-week time-specific high-intensity interval training (Chrono-HIIT) programme among low-physically active Chinese college students with an intermediate chronotype. The primary objective of this feasibility pilot randomized controlled trial is to assess the practicality and acceptability of implementing the intervention, including participant recruitment, retention, adherence, safety, and data completeness. The secondary objective is to explore the preliminary effects of morning versus evening HIIT on health-related physical fitness outcomes, including body composition, cardiorespiratory fitness, muscular strength, muscular endurance, and flexibility. In addition, the qualitative component of the study aims to explore participants’ experiences, perceived benefits, barriers to participation, and overall acceptability of the intervention. It is hypothesized that the Chrono-HIIT programme will demonstrate acceptable feasibility and adherence among low-physically active Chinese college students and may produce preliminary improvements in health-related physical fitness outcomes. The findings may contribute to the optimization of physical education programmes and inform the design of future large-scale randomized controlled trials aimed at promoting efficient and sustainable physical activity interventions in college settings.

## 2. Materials and Methods

### 2.1. Study Design

This study is designed as a feasibility pilot randomized controlled trial, consistent with CONSORT extension guidelines for pilot and feasibility studies consisting of two sequential phases: (1) a quantitative feasibility trial and (2) a qualitative exploration of participant experiences with the intervention. The protocol has been developed and reported in accordance with the Standard Protocol Items: Recommendations for Interventional Trials (SPIRIT) guidelines, which provide a standardized framework for reporting clinical trial protocols.

The study will be conducted at Qiqihar University, Qiqihar, China. In Phase I, eligible participants will be randomly allocated to one of three groups: Morning HIIT, Evening HIIT, or Control group, using a restricted lottery-based randomisation method with allocation concealment. Randomisation will be conducted after eligibility confirmation, written informed consent, and completion of baseline assessments. Identical opaque sealed envelopes containing group assignments will be prepared by an independent researcher and selected by participants at the point of allocation. Participants in the intervention groups will complete an eight-week high-intensity interval training (HIIT) programme, with the primary distinction between groups being the timing of the training sessions (morning or evening). Participants in the control group will continue their usual daily routines without participating in the structured exercise programme during the study period.

Due to the nature of the exercise intervention, participants and exercise instructors cannot be blinded to group allocation. Therefore, the present study will adopt an assessor-blinded design. Outcome assessors and data analysts will remain blinded to participant allocation where feasible to minimize potential assessment and analytical bias throughout the study period.

Phase II will involve a qualitative investigation aimed at exploring participants’ experiences with the intervention. A purposive sample of participants who completed the intervention will be invited to participate in semi-structured interviews to explore perceptions of the HIIT programme, including its feasibility, acceptability, perceived benefits, and potential barriers to participation.

Approval to conduct the study at Qiqihar University was obtained prior to participant recruitment and data collection. This approval was granted through the Qiqihar University Experimental Application Form, dated 6 June 2024, with institutional endorsement provided on 10 June 2024. The document did not include a formal approval reference number. As the study forms part of a doctoral research project undertaken under the academic supervision of Universiti Kebangsaan Malaysia, formal research ethics approval was subsequently obtained from the Universiti Kebangsaan Malaysia Research Ethics Committee (Approval No. JEP-2025-206). The study was also registered with the Thai Clinical Trials Registry (Registration No. TCTR20250607005). All participants will provide written informed consent before enrolment, and the study will be conducted in accordance with the principles of the Declaration of Helsinki.

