### 2.3. Sample Size

Sample size estimation for the pilot trial was guided by the recommendations of Whitehead et al., [15] for pilot randomized trials. These recommendations indicate that pilot studies should recruit sufficient participants to provide preliminary estimates of effect size that can inform the sample size calculation for a subsequent definitive trial.

Based on these guidelines, approximately 15–25 participants per group are considered adequate for pilot trials investigating continuous outcomes with moderate effect sizes. Therefore, the present study aims to recruit approximately 72 participants in total, with 24 participants allocated to each study group (morning HIIT, evening HIIT, and control).

For the qualitative component, interview-based studies typically achieve data saturation with 9–17 participants [16]. Therefore, approximately 10–15 participants will be purposively selected for interviews. Additional interviews will be conducted if new themes continue to emerge during analysis.

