### 2.10. Qualitative Interviews

Semi-structured interviews will be conducted with a subset of participants from the intervention groups to explore their perceptions and experiences regarding the HIIT module [30]. Semi-structured interviews allow participants to describe their experiences in depth while enabling the researchers to systematically explore key aspects of the intervention.

The interview questions will be developed based on previous qualitative research examining exercise intervention experiences [31]. The interview guide will focus on several core domains, including participants’ overall experiences with the intervention, perceived physical responses, psychological effects, perceptions of the training design, and suggestions for improving the programme. The detailed interview guide is presented in Table 3.

Participant recruitment for the interviews will follow the data saturation approach described by Francis [32]. Initially, 10 participants will be interviewed. Following the completion of these interviews, the data will be analysed to determine whether new themes continue to emerge. If additional themes are identified, three further interviews will be conducted. This process will continue in increments of three participants until no new themes emerge from the data, indicating that thematic saturation has been achieved.

To ensure a balanced representation of perspectives, the study will also aim to maintain gender balance among interview participants, targeting an approximate 1:1 male-to-female ratio. This approach is intended to account for potential gender-related differences in exercise perceptions and experiences [33].

Prior to the interviews, participants will be provided with clear information regarding the purpose of the study, interview procedures, and the intended use of the collected data. Written or verbal informed consent will be obtained before participation. Participants will also be informed that their participation is voluntary and that they may withdraw from the interview at any time without any negative consequences.

To ensure confidentiality and protect participant privacy, strict data protection procedures will be implemented. All interview recordings, transcripts, and related materials will be securely stored, and participants’ identities will be anonymized using unique identification codes rather than personal names.

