## 4. Conclusions

This protocol describes a mixed-methods feasibility randomized controlled trial designed to examine the feasibility and potential effectiveness of a HIIT module for improving health-related physical fitness among Chinese college students. The study will also explore the influence of exercise timing and participants’ experiences with the intervention. The findings will provide preliminary evidence to inform the design of future large-scale trials and support the development of practical and time-efficient physical activity interventions in university settings.

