**Figure 2 healthcare-14-01443-f002:**
[figure not shown]
CONSORT Flow Diagram for the Chrono-HIIT Study.

**Table 1 healthcare-14-01443-t001:** SPIRIT (Standard Protocol Items: Recommendations for Interventional Trials) schedule of enrolment, interventions, and assessment.

Timepoint	Study Period										
	Enrolment	Allocation	Post-Allocation								Close-Out
	2/2026–3/2026	2/2026–3/2026	Week 1	Week 2	Week 3	Week 4	Week 5	Week 6	Week 7	Week 8	5/2026
Enrolment											
Screening	√										
Eligibility	√										
Informed consent	√										
Allocation		√									
Intervention morning group			√	√	√	√	√	√	√	√	
Intervention evening group			√	√	√	√	√	√	√	√	
Control group			√	√	√	√	√	√	√	√	
Assessments											√
Health-related physical fitness		√								√	

**Table 2 healthcare-14-01443-t002:** Detail protocol.

Time	Movements
0:00–0:40	High Knees
0:40–1:00	Rest
1:00–1:40	Jumping lunges
1:40–2:00	Rest
2:00–2:40	Jumping Jacks
2:40–3:00	Rest
3:00–3:40	Bodyweight Squats
3:40–4:00	Rest
4:00–4:40	Burpees
4:40–5:00	Rest
5:00–5:40	Butt kicks
5:40–6:00	Rest
6:00–6:40	Push ups
6:40–7:00	Rest
7:00–7:40	Mountain Climbers
7:40–8:00	Rest

**Table 3 healthcare-14-01443-t003:** Interview guide.

No.	Interview Question
1.	Please describe your experience participating in the HIIT course.
2.	What was the most memorable movement for you throughout the entire module? Why?
3.	During the training, what specific physical changes did you notice? (e.g., fatigue level, heart rate, amount of sweating, muscle sensation)
4.	What impact do you think the HIIT has had on your physical fitness, endurance, or overall physical condition?
5.	How did you typically feel emotionally after participating in HIIT? (e.g., excited, stressed, focused, bored).
6.	During or after the training, did you experience any changes in your sense of accomplishment, motivation, self-confidence, or willpower? Please describe specifically
7.	Were there moments when you felt anxious, apprehensive, or wanted to give up? How did you cope with them?
8.	Do you think the current structure, duration, intensity, and movement arrangement of the HIIT module are reasonable? Why?
9.	What do you think are the advantages and potential disadvantages of this training method, respectively?
10.	Regarding safety, what areas do you think require special attention or need more guidance?
11.	Do you have any suggestions?

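### Interviews on barriers and acceptability admit completers only, are balanced on sex but not on training time, and do not systematically ask about session time or missed sessions

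*Protocol article*

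**What the plan says.** **Who is interviewed.** Section 2.1 sets the condition for Phase II: "A purposive sample of participants who completed the intervention will be invited to participate in semi-structured interviews". Section 2.10 names the arms: "Semi-structured interviews will be conducted with a subset of participants from the intervention groups". It does not repeat the condition and makes no provision for people who stopped.

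**Why they are interviewed.** The Introduction states that "the qualitative component of the study aims to explore participants’ experiences, perceived benefits, barriers to participation, and overall acceptability of the intervention". Section 2.1 repeats the interest in barriers in the very sentence that limits the sample to completers.

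**How many, and how balanced.** Section 2.3: "approximately 10–15 participants will be purposively selected for interviews". Section 2.10 starts with 10 interviews and adds three at a time until no new theme appears, judged on one pooled sample. The only balancing factor is in the same section, which aims to "maintain gender balance among interview participants, targeting an approximate 1:1 male-to-female ratio".

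**What is asked.** Section 2.10 refers the reader to Table 3 for the detailed guide of 11 questions. The item closest to the design of the sessions is item 8: "Do you think the current structure, duration, intensity, and movement arrangement of the HIIT module are reasonable", followed by a request for reasons.

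**The concern.** An interview study of barriers needs to hear from people whom the barriers affected. Under section 2.1 a student who left because the sessions clashed with classes, came too early, or were too hard cannot be chosen. Those who remain have, by definition, coped with whatever barriers they met. The accounts collected are therefore likely to under-report barriers and to sound more favourable than the experience of all who were allocated.

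The second part concerns timing. Section 2.1 makes time of day the main difference between the morning and evening arms. The Introduction lists the influence of timing on perceptions and experiences among the open questions, and the Discussion gives the feasibility and acceptability of training at different times of day as the gap the trial addresses. Section 2.2 expects class timetables and shortage of time to be barriers. The guide puts no question on any of this, and nothing in the stated sampling makes sure that both arms are adequately heard.

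What is at stake is the use of the pilot. If attendance differs between morning and evening, the attendance records will show it. The plan then has no designed way to learn why, which is what is needed to refine the intervention for the definitive trial.

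**Working it through.** The plan gives no figure for this point, so there is none to reproduce. The check has four steps.

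**1. How many people the completer rule can exclude.**
- Inputs: 24 per arm (section 2.3), so 24 + 24 = 48 in the HIIT arms; retention acceptable if more than 80% complete (section 2.9.1).
- With k non-completers the condition is (48 − k)/48 > 0.80.
- k = 9: 39/48 = 81.25%, met. k = 10: 38/48 = 79.2%, not met. The largest k is 9, or 9/48 = 18.75% of the HIIT participants.
- Within one arm: 20/24 = 83.3%, so at most 4.
- Assumption: the criterion is applied to the HIIT arms. Section 2.9.1 does not name the arms. Over all 72 participants it would allow 14 (58/72 = 80.6%), with no statement of how they may fall between arms.

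**2. Direction and possible size of the tilt.** Interviews do not estimate a proportion, so this is only an illustration with assumed values. Let r be the share completing, a the share of completers who find the programme acceptable, and b the same share among those who stopped. Completers alone overstate acceptability by a − [r·a + (1 − r)·b] = (1 − r)(a − b).
- r = 0.8125, a = 0.9, b = 0.2: 0.1875 × 0.7 = 0.131.
- r = 0.8125, a = 0.9, b = 0.5: 0.1875 × 0.4 = 0.075.
- r = 0.90, a = 0.9, b = 0.2: 0.10 × 0.7 = 0.07.
- r = 0.90, a = 0.9, b = 0.5: 0.10 × 0.4 = 0.04.
- r = 1: 0.

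On these assumptions the tilt runs from nil to about 13 percentage points. It disappears if nearly all complete, or if those who stopped think as the others do.

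**3. Reading the guide item by item.** The 11 items of Table 3 cover: overall experience (1), most memorable movement (2), bodily changes (3), perceived effect on fitness (4), emotions afterwards (5), motivation and confidence (6), wanting to give up and how this was handled (7), design of the module (8), advantages and disadvantages (9), safety (10), suggestions (11). Items that name morning, evening, time of day, timetable, sleep or missed sessions: 0 of 11. Item 8 lists four features of the design, and time of day is not one of them. Item 7 comes nearest to drop-out, but its follow-up suits someone who carried on.

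**4. Whether a remedy fits the planned number.** Balance by training time fits: 5 morning and 5 evening among the first 10. Judging saturation separately in each arm does not fit. The rule of 10 followed by steps of three, applied twice, needs at least 2 × 10 = 20 interviews, against a planned 10–15.

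**The case against.** Several stronger readings are tempting, and the document does not support them.

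- *Interviews are the only source on acceptability.* A reader might infer this because there is no acceptability questionnaire. The Introduction, however, places recruitment, retention, adherence, safety and data completeness under practicality and acceptability. The drop-out and attendance of non-completers therefore already count. What is missing is their account of the reasons.
- *The interviews will be silent on timing.* They are semi-structured. Items 1, 7, 8, 9 and 11 leave room for a participant to raise session time, and interviewer probes may exist outside the article. What stands is that the published guide does not ask about it systematically. The Conclusions should not be pressed here either: "The study will also explore the influence of exercise timing" is followed in the same sentence by participants' experiences as a separate item, so it does not promise that the interviews will compare times of day.
- *The findings will be biased.* This is an expected direction, not a certainty. Moreover, completion is not tied to the attendance rule of more than 70%, so low attenders who stay to the end may still be eligible.
- *Sections 2.1 and 2.10 contradict each other.* Completers are a subset of the intervention groups, so the two sentences can be read together. It would still help to state one frame in both places.
- *Imbalance between arms can be given a probability.* Drawing 10 at random from 24 + 24 leaves one arm with 3 or fewer in 29% of draws (5% at 13 interviews, 1% at 15). But the sampling is purposive, so these figures do not describe the plan, and nothing in the document shows that three interviews in an arm are too few.

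It is also fair to say that the stated qualitative aim does not mention a comparison of morning with evening, and that the secondary objective addresses timing through fitness outcomes. This weakens the timing part but does not remove it, given the gap described in the Introduction and the Discussion.

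**Conclusion.** The point holds in a limited form. The completer-only rule in section 2.1 works against the stated aim of learning about barriers. It excludes up to 9 of 48 HIIT participants in a trial that meets its retention criterion, if that criterion is applied to the HIIT arms. The likely effect is a tilt towards favourable views, of a size that depends on how many stop and why. The guide does not systematically ask about session time, fit with timetable or sleep, or missed sessions, and the sample is balanced on sex but not on training time, although time of day is what mainly separates the arms.

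These are choices the article states, not details left to a fuller document. The randomised comparison and the quantitative feasibility criteria are unaffected. The change is worth making because it is cheap and serves the purpose of the pilot.

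**What to change.** 1. In sections 2.1 and 2.10, use one sampling frame: a purposive sample of all participants allocated to morning or evening HIIT. Include some who stopped, or who attended 70% of sessions or fewer, where they agree. With three sessions a week for eight weeks (24 sessions), the latter means 16 or fewer (16/24 = 66.7%; 17/24 = 70.8%).
2. Add a target of roughly equal morning and evening numbers, alongside the balance on sex, within the planned 10–15 interviews. Keep saturation judged on the pooled sample.
3. Add two questions to Table 3: one on how the allocated session time fitted with classes and sleep, and one on the reasons for missing sessions or stopping.

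Cost: a few sentences and two questions, with no change to the planned number of interviews. People who stopped are harder to reach, so no fixed number of them can be guaranteed, and the revised guide may need to be notified to the ethics committee. If the interviews have already been done, state completer-only sampling as a limitation; the limitations in the Discussion do not mention it at present.
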